As with other bariatric procedures, patients can struggle with recurrent weight gain after initially optimal OAGB [12]. As mentioned before, addressing weight gain is a complex and multifaceted challenge. In some cases, revisional MBS is considered an option, but some of these revisional procedures are associated with a considerably high risk of complications and often yield unsatisfactory outcomes [9]. The most commonly known revisional procedures are conversion from the gastric band or sleeve to a gastric bypass, limb lengthening of a gastric bypass, or pouch revision including revision of the gastro-jejunal anastomosis. A new alternative to the abovementioned revisional procedures involves longitudinal reduction of the pouch (or sleeve) and placement of a non-adjustable silicone ring around the gastric pouch. This technique may also lead to more significant weight loss and a reduced risk of long-term recurrent weight gain [13, 14]. Given the challenges posed by recurrent weight gain, it seems more reasonable to pursue all possible ways of reducing the risk of recurrent weight gain at the time of the primary procedure.

While studies have suggested the effectiveness of silicone rings in combination with primary RYGB, there is a lack of data on their use with primary OAGB [14]. Although the OAGB and RYGB share similar mechanisms of action, they differ in certain anatomical aspects such as pouch dimensions. Traditionally, the RYGB with a small pouch is considered to have a more restrictive nature, while the OAGB, with its longer and narrower pouch, is thought to be more hypo-absorptive. However, recent studies have introduced successful modifications to the RYGB, such as a longer pouch and an extended biliopancreatic limb, which resemble some of the characteristics of the OAGB [15]. Conversely, the addition of a silicone ring to the OAGB may enhance restriction, addressing a potential limitation in the original procedure. To date, no randomized studies have provided (long-term) data on the effectiveness of primary banded OAGB.

The RiMini trial aims to investigate whether incorporating a silicone ring during primary OAGB improves weight reduction, measured as %TWL 5 years after surgery, compared to classic OAGB. Secondary endpoints include changes in obesity complications, quality of life, and adverse events related to surgical procedures.

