### Secondary Outcomes

%EWL: defined as the percentage of excess weight lost relative to the excess weight at the time of informed consent [22]. In formula$${\%EWL}=\frac{\text{preoperative BMI}-\text{ current BMI}}{\text{preoperative BMI}-25}\text{x}\;100$$Reduction or remission of obesity complications: Obesity complications include type 2 diabetes mellitus, hypertension, joint complaints, dyslipidemia, OSAS, and GERD. (Inter)national guidelines are used as reference [23, 24]. Reduction is defined as a decrease in symptoms, medication use and/or dosage, and/or laboratory results. Remission is defined as the state in which a patient no longer reports symptoms, does not require any medication for their comorbidity, and/or has normalized laboratory results. In case of type 2 diabetes, remission is defined if glycosylated hemoglobin (HbA1c) is 43 mmol/mol without the use of pharmacotherapy as per local protocol [23] In case of OSAS, remission is considered when there is a discontinuation of CPAP treatment.Quality of life: assessed using the SF-36, OBESI-Q, and GERD-HQoL questionnaires at earlier mentioned follow-up intervals compared to pre-operative baseline measurements.Presence of early and late dumping: determined based on symptoms reported by patients and evaluated by expert physicians during the follow-up period.Complications: All complications during follow-up and until 5 years postoperative are included in the analysis, regardless of their potential relation to the ring. Complications are categorized as perioperative, early (< 30 days, with or without readmission), and late (> 30 days, with or without readmission). Possible complications include bleeding, wound infections, intra-abdominal abscesses, anastomotic leaks, deficiencies (especially in vitamin B12 and ferritin), conversions, migration, erosion, and slipping of the ring. Laboratory reference values are used for deficiencies.

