### Statistical Analysis

IBM’s Statistical Package for the Social Sciences (SPSS) is utilized for the statistical analyses of the obtained data. Histograms (visual inspection) are used to ascertain whether variables are normally distributed. A significance level (alpha) of 0.05 is applied to all analyses unless stated otherwise. Differences in baseline characteristics of the study groups are tested using the independent *t*-test (for continuous, normally distributed data), the Mann–Whitney test (for non-normally distributed or ordinal data), or the chi-square test (for categorical data).

Assumptions for linear regression will be checked for all outcomes, including normality of residuals and homogeneity of variances. Where necessary, transformations (e.g., log transformation) were applied to meet model assumptions.

Difference between groups in %TWL, %EWL, and GERD-HRQoL at 5 years postoperative will be assessed using the independent *t*-test or Mann–Whitney test (for normally or non-normally distributed data, respectively). Baseline characteristics related to both the type of surgery and outcome variables (with *p*-value < 0.15) will be considered confounders in the analyses. If one or more confounders are identified, linear regression models will be used to assess differences between groups in %TWL, %EWL, and GERD-HRQoL at 5 years postoperative, each adjusted for relevant confounders.

The difference between groups in the reduction of obesity complications at 5 years postoperative will be tested using chi-square tests for each comorbidity. Holm-Bonferroni correction will be used to correct for multiple testing.

Chi-square tests will be used for the difference between groups in change of scores of the questionnaires, early and late dumping, and reflux. Additionally, a linear mixed model analysis will test the difference in change in the subscales of the SF-36 and OBESI-Q over time between groups.

The difference in the total number of complications between groups will be tested with independent *t*-tests or Mann–Whitney tests (for normally or non-normally distributed data, respectively).

Missing data will be reported if known. A sensitivity analysis will be performed for the primary outcome: analysis of the data “as-is” (without imputation) will be compared with the results of the analysis where missing data is imputed.

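### The GERD comorbidity test looks only for reduction at 5 years, so it cannot show worsened or new-onset GERD, and its definition does not separate remission after conversion or ring removal

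*Protocol article*

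**What the plan says.** All places are in the protocol article.

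- **Introduction:** "Secondary endpoints include changes in obesity complications, quality of life, and adverse events related to surgical procedures".
- **Secondary Outcomes:** "Obesity complications include type 2 diabetes mellitus, hypertension, joint complaints, dyslipidemia, OSAS, and GERD". Two outcomes are then defined. The first: "Reduction is defined as a decrease in symptoms, medication use and/or dosage, and/or laboratory results". The second: "Remission is defined as the state in which a patient no longer reports symptoms, does not require any medication for their comorbidity, and/or has normalized" (the sentence ends by referring to laboratory values). Diabetes and OSAS get their own remission rules; GERD does not.
- **Statistical Analysis, comorbidities:** "The difference between groups in the reduction of obesity complications at 5 years postoperative will be tested using chi-square tests for each comorbidity", with a Holm-Bonferroni correction.
- **Statistical Analysis, other reflux measures:** "Difference between groups in %TWL, %EWL, and GERD-HRQoL at 5 years postoperative will be assessed using the independent *t*-test or Mann–Whitney test"; and "Chi-square tests will be used for the difference between groups in change of scores of the questionnaires, early and late dumping, and reflux". The linear mixed model over time names the SF-36 and OBESI-Q subscales but not GERD-HRQoL.
- **Outcome Measurement:** every outcome is recorded at 4 months and then yearly to year 5.
- **Secondary Outcomes, complications:** all complications to 5 years count, whether or not related to the ring. Conversions and ring migration, erosion and slipping are named as examples; ring removal and new reflux are not. The test is on the total number per group.
- **Table 1:** only clinically severe, therapy-resistant GERD is excluded, so patients with milder GERD or none can enter.

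**The concern.** Change can go either way, but the GERD outcome as defined and tested has only a favourable direction. A patient whose GERD worsens falls in the same cell as one whose GERD is unchanged. A patient who develops GERD either falls outside the denominator or is grouped with patients who never had it; the article does not say which.

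The definition also looks only at status. It does not ask how a patient came to be free of symptoms, so relief after a conversion or ring removal meets the same definition as relief without reoperation.

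Reflux has its own questionnaire and its own exclusion criterion in this trial, so the sponsor evidently regards it as important. What is at stake is whether the GERD comorbidity result can be read as a statement about harm as well as benefit. As written, it cannot.

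**Working it through.** **1. The plan's own figure.** The only relevant number stated is the evaluable sample. With a difference of 5, SD 10, two-sided alpha 0.05 and power 80% (Sample Size Calculation):

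n = 2 × (1.960 + 0.842)² × 10² / 5² = 62.8, so 63 per group.

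This reproduces (the exact t-test gives 63.77, so 64; power at 63 is 0.795). With 40% loss, 63 / 0.60 = 105 per group, 210 in total. These figures concern %TWL. The article states no GERD, reflux or reoperation rate.

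**2. Patient courses under the stated definitions** (a decrease is taken to mean relative to baseline, which is an assumption).

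| Course | Reduction test at year 5 | GERD-HRQoL at year 5 |
|---|---|---|
| A. No GERD at baseline or year 5 | not in test, or no reduction | low |
| B. No GERD at baseline, GERD at year 5 | same as A | raised |
| C. Baseline GERD, unchanged | no reduction | unchanged |
| D. Baseline GERD, worse | same as C | higher |
| E. Baseline GERD, worsens, conversion or ring removal, no symptoms or medication at year 5 | reduction (meets remission) | low |
| F. Baseline GERD, resolves without reoperation | same as E | low |

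The reduction test cannot tell A from B, C from D, or E from F. The 5-year GERD-HRQoL score separates the first two pairs but not E from F. The reflux test and the test on change in questionnaire scores might help, but neither has stated categories or a stated time point. In course E a conversion adds one event to the complication total, with no link to reflux. The mixed model would use scores from before the reoperation, but GERD-HRQoL is not in it.

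**3. Sensitivity of the reduction rate (illustration).** Assumed: 63 evaluable per arm, baseline GERD of 20%, 30% or 40%.

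| Baseline GERD | Patients who can show reduction, per arm | Shift per patient classified differently | Shift for three | Patients without GERD to reduce |
|---|---|---|---|---|
| 20% | 63 × 0.20 = 12.6, about 13 | 1/13 = 7.7 points | 23.1 | 50 |
| 30% | 63 × 0.30 = 18.9, about 19 | 1/19 = 5.3 points | 15.8 | 44 |
| 40% | 63 × 0.40 = 25.2, about 25 | 1/25 = 4.0 points | 12.0 | 38 |

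The last column is the group in which new GERD cannot appear as harm in this test.

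**4. What a new-onset comparison could detect.** Among the m patients per arm without baseline GERD, with p̄ the mean of p1 and p2:

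power = Φ{ [ |p2 − p1| − 1.96 √(2p̄(1 − p̄)/m) ] / √[ (p1(1 − p1) + p2(1 − p2))/m ] }

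For assumed rates of 5% and 15% and m = 50: (0.100 − 1.96 × 0.0600) / 0.0592 = −0.297, so power is 0.38. For m = 44 and 38 it is 0.34 and 0.30. For 5% against 20% it is 0.62, 0.57 and 0.51. The comparison is best reported as a difference with its confidence interval; a non-significant result would not show absence of harm.

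**The case against.** The strongest reply is that reflux is not assessed through this one test. GERD-HRQoL is a graded score that can show new or worse symptoms at year 5. A chi-square on change in questionnaire scores and another on reflux are planned, and neither is limited to year 5. Status is recorded at every visit, so worsening before a reoperation would be in the data. All of this stands. It confines the point to the comorbidity endpoint and to what the other analyses are not stated to do.

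A reader might infer that the plan deliberately counts patients converted for reflux as improved, and so is biased towards calling the ring safe. The document does not support that. It gives no rule for scoring GERD after reoperation; that such a patient meets remission follows from the wording of the definition, and a full protocol or analysis plan may add a rule. Conversions are also counted as complications, so the event is not hidden. The definition is the same in both arms. Ring removal is possible only with a ring, but a net bias would need more reflux-driven reoperations in that arm, and no rate is given for either.

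It can also be said that status at year 5, however reached, is a legitimate question. That is right, and it argues against scoring every reflux reoperation as worsened in the main analysis. Doing so would change the estimand and require a cause to be assigned to each reoperation in a non-blinded trial.

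What the reply does not remove is the mismatch between an aim of describing changes and a stated endpoint that records only improvement.

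**Conclusion.** The concern holds in a limited form. The GERD comorbidity test, as the article fixes it, cannot show worsened or new-onset GERD, and its definition does not separate remission with and without reoperation. The other stated analyses partly cover reflux present at year 5. None is stated to capture reflux that ended through reoperation.

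Neither the size nor the direction of any bias can be derived from the document. The shift of 4.0 to 7.7 points per patient rests on assumed baseline GERD of 20% to 40% among 63 evaluable patients per arm. It shows only that the reduction rate would rest on small numbers. The primary endpoint and sample size are unaffected.

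**What to change.** 1. In Secondary Outcomes, classify GERD in all randomised patients with follow-up as remission, reduction, unchanged, worsened or new-onset. In Statistical Analysis, compare the proportion worsened or new-onset between arms, with a confidence interval. This can serve as the definition of the reflux chi-square already planned.
2. Add a sensitivity analysis in which any patient with a conversion or ring removal before year 5, whatever the reason, is not counted as GERD reduction or remission. No cause has to be assigned. The year-5 status analysis remains the main one.
3. Add GERD-HRQoL to the linear mixed model planned for SF-36 and OBESI-Q, so that scores from 4 months onward are used.

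**Cost.** GERD status, GERD-HRQoL and conversions are already planned outcomes; ring removals must be identifiable in the records. There would be one or two more secondary comparisons, and the text should say whether they fall under the Holm-Bonferroni correction. The sensitivity analysis also counts reoperations unrelated to reflux as failures, and ring removal can occur only where a ring was placed. It should therefore be read as a check on the main result and not replace it.

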### Quality of Life

Participating patients are asked to complete three questionnaires pre- and postoperatively during the follow-up period, the SF-36, OBESI-Q, and GERD-HRQoL, to assess quality of life.

The SF-36 questionnaire includes 36 items and measures eight health concept scales: Physical Functioning, Role-Physical, Bodily Pain, General Health, Vitality, Social Functioning, Role-Emotional, and Mental Health. The raw scores of each subscale are transformed to a 0–100 scale, where higher scores indicate better functioning or well-being. A minimum of 50% of the items in each subscale must be answered to yield a viable result [17].

The OBESI-Q questionnaire includes a set of six selected subscales from the BODY-Q that have been individually validated for Dutch practice [18, 19]. The BODY-Q measures four overarching domains. Each domain includes four or more independently functioning scales. Scales chosen in OBESI-Q include eating behavior, social, psychological, physical function, body image, and sexual. Scores for each outcome are calculated by summing up the points for each subscale. To enhance the interpretability of the sum score, it is converted to a total score on a scale of 0 to 100, where higher scores indicate better functioning or well-being.

The GERD-HRQoL questionnaire includes 18 items to measure the impact of GERD on sleep, exercise, diet, need for medication, sex life, work, social activity, and psychological well-being [20]. The total score is calculated by summing up the individual item scores, with no transformation of the raw scores into a scaled score required. The optimal score is 0, which indicates that the individual is asymptomatic across all categories, while the lowest possible score is 50, indicating complete incapacitation in all categories.

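### Chi-square tests are named for changes in numeric questionnaire scores, with no categories of change stated; for GERD-HRQoL change this is the only test named

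*Protocol article*

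**What the plan says.** The Quality of Life section defines numeric scores. For each SF-36 subscale, "The raw scores of each subscale are transformed to a 0–100 scale". For OBESI-Q the sum score is rescaled: "it is converted to a total score on a scale of 0 to 100". GERD-HRQoL is an untransformed sum running from 0 (no symptoms) to 50 (worst).

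The Secondary Outcomes section makes change from baseline the quality-of-life outcome for all three instruments, ending with "GERD-HQoL questionnaires at earlier mentioned follow-up intervals compared to pre-operative baseline measurements". Outcome Measurement sets the visits at 4 months and then yearly to 5 years.

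The Statistical Analysis section assigns these tests:

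- All questionnaires, change: "Chi-square tests will be used for the difference between groups in change of scores of the questionnaires, early and late dumping, and reflux".
- SF-36 and OBESI-Q, change over time: "Additionally, a linear mixed model analysis will test the difference in change in the subscales of the SF-36 and OBESI-Q over time between groups".
- GERD-HRQoL, level at 5 years: "Difference between groups in %TWL, %EWL, and GERD-HRQoL at 5 years postoperative will be assessed using the independent" t-test, or the Mann-Whitney test if the data are not normal. If confounders are identified, "linear regression models will be used to assess differences between groups in %TWL, %EWL, and GERD-HRQoL at 5 years postoperative".

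For baseline comparisons the same section gives chi-square to categorical data, the t-test to normal continuous data and Mann-Whitney to ordinal or non-normal data.

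**The concern.** A chi-square test compares how often patients fall into categories. The article states no categories of change for any questionnaire: no responder threshold, and no grouping into improved, unchanged and worse. As written, the named test and the named quantity do not match, and the sentence departs from the rule the section itself uses at baseline.

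Two things are at stake, both among secondary outcomes. First, SF-36 and OBESI-Q change has two analyses that can disagree, and the text does not say which one counts. Second, GERD-HRQoL change from baseline, which the outcome definition includes, has no fitting test. The plan would be followed either by grouping the scores, which discards information and needs cut-offs the article does not give, or by tabulating raw score values, which makes the table too sparse.

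**Working it through.** **1. Which test covers which quantity** (from the Statistical Analysis section)

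| Instrument | Scale | Change from baseline | Level at 5 years |
|---|---|---|---|
| SF-36 | 0-100 | chi-square, plus mixed model | none separately |
| OBESI-Q | 0-100 | chi-square, plus mixed model | none separately |
| GERD-HRQoL | 0-50 | chi-square only | t-test or Mann-Whitney; regression if confounders are found |

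The baseline GERD-HRQoL score would enter the 5-year regression only if it passed the confounder screen, that is, if it were related to both arm and outcome at p < 0.15. The plan does not ensure that baseline is taken into account.

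**2. The plan's own figure.** The Sample Size Calculation concerns %TWL only: difference 5, SD 10, two-sided alpha 0.05, power 80%.

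- n per arm = 2 × (1.960 + 0.842)² × 10² / 5² = 62.8, so 63. This reproduces the stated figure. Exact t-test power at 63 per arm is 79.5%.
- 63 / (1 − 0.40) = 105 per arm, 210 in total. This also reproduces.

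Neither figure is affected by this point.

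**3. Illustration: change cut into two categories.** The article gives no effect size, SD or cut-off for any questionnaire. Assumptions: 63 evaluable patients per arm (borrowed from the %TWL calculation), normal change scores with SD 1, and means 0 and d. With cut-off c:

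- p1 = 1 − Φ(c), p2 = 1 − Φ(c − d), p̄ = (p1 + p2)/2
- power = Φ{ [ (p2 − p1) − 1.96 × √(2p̄(1 − p̄)/n) ] / √( [p1(1 − p1) + p2(1 − p2)]/n ) }

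Worked case, d = 0.5 and c = 0.25: p1 = 0.401, p2 = 0.599, p̄ = 0.5. The pooled standard error is √(0.5/63) = 0.0891 and the unpooled one is 0.0873. Power = Φ[(0.1974 − 1.96 × 0.0891)/0.0873] = Φ(0.26) = 0.603.

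| d | t-test power | c | p1, p2 | chi-square power | n per arm for 80%, chi-square (t-test) |
|---|---|---|---|---|---|
| 0.5 | 79.5% | 0.25 | 0.401, 0.599 | 60.3% | 100 (63) |
| 0.5 | 79.5% | 0.5 | 0.309, 0.500 | 59.3% | 102 (63) |
| 0.5 | 79.5% | 1.0 | 0.159, 0.309 | 51.1% | 124 (63) |
| 0.5 | 79.5% | −0.5 | 0.691, 0.841 | 51.1% | 124 (63) |
| 0.3 | 38.6% | 0.15 | 0.440, 0.560 | 26.6% | 275 (175) |
| 0.3 | 38.6% | 0.5 | 0.309, 0.421 | 25.6% | 288 (175) |
| 0.3 | 38.6% | 1.0 | 0.159, 0.242 | 21.3% | 362 (175) |
| 0.3 | 38.6% | −0.5 | 0.691, 0.788 | 23.3% | 323 (175) |

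The loss runs from 38.6 − 26.6 = 12 points to 79.5 − 51.1 = 28 points.

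**4. Illustration: scores left uncut.** Simulation of 4,000 trials per setting, 63 per arm, SD 20, change rounded to 5-point steps (about 20 distinct values). About 73-74% of expected cell counts fall below 5. Chi-square rejects in 2.5% of trials with no difference and in 16% at d = 0.5; the t-test rejects in 4.9% and 80%.

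**The case against.** The strongest reply is that every instrument already has a suitable analysis of some kind. SF-36 and OBESI-Q change goes to a mixed model in the very next sentence, and 5-year GERD-HRQoL goes to a t-test or Mann-Whitney test. Under randomisation, comparing 5-year scores is a valid comparison of the arms; leaving out baseline costs precision, not validity. All of this stands. A reader might infer that the quality-of-life results hang on a cut-point chosen after seeing the data, or that GERD-HRQoL has no valid analysis. The article supports neither: the mixed model and the 5-year test need no cut-point.

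It can also be said that a fuller plan may define responder categories, and that three ordered groups would suit a chi-square test. That is possible. But the sentence names a test for change of scores, not for responder status, so the mismatch lies in what the text says and not in a detail left out.

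The power figures are fairly open to challenge, since 63 per arm and 0.5 SD come from the %TWL calculation. They are kept only as an illustration with stated assumptions. They do not describe the mixed model or the 5-year GERD-HRQoL test, neither of which dichotomises.

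Finally, a linear mixed model is not automatically right for GERD-HRQoL. The score has a floor at 0 and severe therapy-resistant GERD is an exclusion criterion, so values may bunch near 0. This also stands, and the fix allows for it.

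**Conclusion.** The point holds in a limited form. Chi-square is named for changes in numeric scores for which no categories are stated. For SF-36 and OBESI-Q it is a redundant second test that may conflict with the mixed model. For GERD-HRQoL it is the only test named for change from baseline, and no fitting analysis is named for the visits before 5 years.

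If the sentence were followed by dichotomising, power would fall from about 80% to 51-60% at a standardised difference of 0.5, and from about 39% to 21-27% at 0.3. This assumes 63 evaluable patients per arm and normal change scores. The size depends on effect and cut-off, neither of which the article gives.

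A reader might go further and argue that most patients improve, so that the categories would sit near a ceiling, or that the ring worsens reflux, so that a safety signal would be lost. The article states neither. It says only that the ring may enhance restriction. The conclusion does not need these claims. Only secondary endpoints are affected.

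**What to change.** 1. Take questionnaire change scores out of the chi-square sentence. Keep chi-square for dumping and reflux, handled as yes/no outcomes.
2. Name the linear mixed model already planned as the analysis of SF-36 and OBESI-Q change, not as an addition to another test.
3. Analyse GERD-HRQoL with its baseline score taken into account, either by adding it to that model or by a baseline-adjusted comparison at 5 years. Provide a transformation or a rank-based alternative in case scores bunch near 0; the section already foresees assumption checks and transformations.

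The cost is a change of wording, slightly more analysis work and a check of model assumptions for GERD-HRQoL. No new data are needed, because all three questionnaires are already completed before and after surgery.

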### Sample Size Calculation

In order to obtain mid-term results, a 5-year follow-up period has been selected, consistent with standard practices in Dutch metabolic bariatric surgery. A total of 63 patients per group is necessary to detect a 5% difference %TWL between groups 5 years post-surgery. This calculation is performed using PASS software, with parameters set at power = 80%, alpha = 0.05, standard deviation = 10%, and average %TWL of group 1 vs. group 2 being 32 vs. 27, assuming a two-sided independent *t*-test.

Jense et al. observed a loss-to-follow-up (LtfU) ranging from 21 to 58% three to five years postoperatively [21]. To have sufficient power for the 5-year analysis, this study takes into account a LtFU of 40%, assuming that actively contacting patients will reduce LtFU at 5 years postoperatively. Based on a required sample of 63 individuals per group and an expected LtFU of 40%, we aim to include 210 patients for this study, 105 per group.

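### The 5-year complication total is tested on raw counts without follow-up time, so the comparison of late events is open to bias if follow-up differs between arms

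*Protocol article*

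**What the plan says.** Statistical Analysis (protocol article) fixes the test: "The difference in the total number of complications between groups will be tested with independent". The sentence goes on to name the t-test where the data look normal and Mann–Whitney where they do not, so the choice between the two depends only on the shape of the distribution.

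Secondary Outcomes sets the counting window: "All complications during follow-up and until 5 years postoperative are included in the analysis, regardless of their potential relation to the ring". It also divides events by time: "Complications are categorized as perioperative, early (< 30 days, with or without readmission), and late (> 30 days, with or without readmission"). The examples listed run from bleeding and anastomotic leaks, through vitamin B12 and ferritin deficiencies, to "conversions, migration, erosion, and slipping of the ring".

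Sample Size Calculation cites loss "ranging from 21 to 58% three to five years postoperatively" and then plans: "this study takes into account a LtFU of 40" per cent, as one figure for both arms.

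No section brings follow-up time, person-years, a rate or censoring into the comparison of complications. The imputation sensitivity analysis in Statistical Analysis covers the primary outcome only.

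**The concern.** A patient's complication count can only grow while the patient is observed. On a raw count, someone lost after 1 year without an event scores zero, the same as someone followed event-free for 5 years. Mann–Whitney in place of the t-test deals with skewness, not with unequal observation.

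The problem lies with the late events. Deficiencies, conversions and ring migration, erosion or slipping can all arise after patients start to drop out. Deficiencies are found by blood tests at the annual evaluations, so their number depends directly on attendance. They also enter the total with the same weight as a leak or an erosion.

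The trial is not blinded and one arm receives an implant, so patients in the two arms could stay in follow-up to different degrees. The arm followed longer would then show more complications at the same true rate. If the ring arm were followed less, a real excess of late ring problems would be diluted. This is the only between-group test that the article gives for complications.

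**Working it through.** **The plan's own figure.** The document gives no size or power for complications. Its loss assumption reproduces: 63 / (1 − 0.40) = 105 per group, 210 in total. The 105 per arm is used below.

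**Inputs.** From the article: 105 per arm, 40% planned loss, cited range 21% to 58%, t-test or Mann–Whitney on total counts. Assumed, because the article does not give them: complication rates, when lost patients leave, and how loss splits between arms.

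**Step 1: raw-count ratio at equal true rates.** Let lost patients be observed for 2 years and the others for 5. Mean follow-up with proportion p retained is 5p + 2(1 − p).

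- 60% in both arms: 5 × 0.60 + 2 × 0.40 = 3.80 years each; ratio 1.00.
- 65% vs 55%: 3.95 / 3.65 = 1.08.
- 70% vs 50%: 4.10 / 3.50 = 1.17.

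A constant loss hazard gives nearly the same answer. With h = −ln(1 − L)/5, mean follow-up is (1 − e^(−5h))/h. That is 3.92 years at 40% loss, 4.21 at 30% and 3.61 at 50%. Loss of 30% vs 50% gives 4.206 / 3.607 = 1.17. The ends of the cited range, 21% vs 58%, give 4.454 / 3.343 = 1.33.

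**Step 2: type I error of the t-test on raw counts** (20,000 simulated trials per setting, Poisson counts, two-year model):

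| Rate per patient-year | 60% / 60% retained | 65% / 55% | 70% / 50% |
|---|---|---|---|
| 0.05 | 5% | 5.6% | 7–8% |
| 0.1 | 5% | 6–6.5% | 10–11% |
| 0.3 | 5% | 8.7% | 20–21% |

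Ranges are from repeated runs. Mann–Whitney behaves alike. The inflation depends strongly on the assumed rate and on the size of the retention gap.

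**Step 3: masking.** Assume a true rate ratio of 1.5 (0.3 per year with the ring, 0.2 without) and a constant loss hazard. The rate test is a Wald test on events per person-year.

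| Loss, ring / control | Raw ratio | Power, t-test | Power, Mann–Whitney | Power, rate test |
|---|---|---|---|---|
| 40% / 40% | 1.51 | 77% | 71% | 83% |
| 50% / 30% | 1.29 | 39% | 29% | 81% |

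**Step 4: would one offset on the pooled total be enough?** Assume 0.30 early events per patient plus 0.03 per year in both arms, with 70% vs 50% retained.

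- Expected counts: 0.30 + 0.03 × 4.10 = 0.423 and 0.30 + 0.03 × 3.50 = 0.405; raw ratio 1.04.
- Per person-year: 0.423 / 4.10 = 0.103 and 0.405 / 3.50 = 0.116; ratio 0.89.

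The pooled rate is further from 1 than the raw count, and in the opposite direction; its type I error is about 9%. An exposure-adjusted test of the late events alone held 4% to 6% in every setting tried. So the early and late periods have to be analysed separately.

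**The case against.** The strongest objection is that the harm is conditional. With equal loss unrelated to complications, the planned test keeps its 5% size and the ratio is right; the cost is some power and understated absolute counts. The article gives one overall loss figure and nowhere predicts a difference between arms. A 20-point gap is also unlikely by chance: with 60% truly retained in both arms, the standard error of the difference is √(2 × 0.6 × 0.4 / 105) = 0.068. A gap of 0.20 is then about 3 standard errors, which occurs in about 0.3% of trials. It would need a systematic cause. All of this stands, and it limits the point to a conditional one.

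The size also depends on the rate: at 0.05 per patient-year the type I error is only 7% to 8% even with that gap. Perioperative and early events are hardly touched by 5-year loss, and the article already sorts events by period. This stands too.

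A reader might infer that the comparison reflects who is lost instead of the effect of the ring. The document does not support that: even with unequal loss, the result reflects ring and loss together. A reader might also take this test for the trial's main safety comparison. The article does not call it that; complications are one of several secondary outcomes.

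Finally, counting all complications is a deliberate choice, and weighting deficiencies equally with surgical events is a separate matter of presentation. The day-30 gap, "early (< 30 days, with or without readmission), and late (> 30 days, with or without readmission"), does not affect the total that is tested. It matters only once early and late events are analysed apart.

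What the objection does not remove is that the article itself fixes a raw-count test for a 5-year outcome with 40% loss expected. This is a stated choice, not detail left to another document.

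**Conclusion.** The point holds in conditional form. The planned test of total complications is valid if follow-up is equal in the two arms and loss is unrelated to complications. It is open to bias if follow-up differs, and the plan has no safeguard against that for this outcome. At 70% against 50% retained, the raw-count ratio at equal true rates is 1.17 and the type I error about 7% to 21% for rates of 0.05 to 0.3 per patient-year. In the other direction, a true ratio of 1.5 can shrink to 1.29, with t-test power of 39%. These figures rest on assumed constant rates, assumed times of loss and an assumed imbalance, none of which is in the article. The exposed part is the late events, including the ring-specific ones. The correction is cheap and worth making, but the primary endpoint is not affected.

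**What to change.** Replace the single test of the total by two comparisons:

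- **Perioperative and early events, up to and including day 30:** counts or proportions in all operated patients.
- **Late events, after day 30:** a negative binomial or overdispersed Poisson model with log follow-up time after day 30 as offset, or time to first late complication with loss to follow-up as censoring.

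Give the rate or hazard ratio with its 95% CI, report follow-up time by arm, and show laboratory deficiencies separately from surgical complications. Assigning day 30 to the early period also closes the gap in the definitions. Do not put one offset on the pooled total, because events that cluster early would then distort the rate.

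The cost is a slightly more complex analysis and no additional patients. It needs event dates and last-contact dates, which the article does not say are recorded; deficiencies can be dated only to the visit at which they are found. It does not cure loss that is itself related to complications, so the report should say so and describe who was lost in each arm.
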